##### **4.4.1. Procedure in the event of premature termination of treatment in the clinical trial**

For all study participants who terminate the study prematurely (drop outs), the reasons for dropping out should be documented if possible. According to the IEHS guidelines, recurrences after TEP or TAPP are treated using the Lichtenstein approach (anterior approach). The

occurrence of a recurrent hernia on one side does not lead to premature termination of the study for this patient, as observation of the hernia on the other side must be continued. Only when a recurrence requiring surgery has also occurred on the other side the study ends for this patient.

#### **4.5. Closure of trial centres/early termination of the clinical trial**

The sponsor is authorised to terminate the trial prematurely due to relevant medical or ethical concerns or lack of feasibility of the trial. In such a case, the reasons for the premature termination of the trial will be documented in detail. Patients who are still undergoing treatment at the time the trial is terminated will continue to be monitored as planned with regard to the occurrence of recurrence (follow-up). If an investigator has ethical concerns regarding the continuation of the trial, this must be reported immediately to the LKP.

Early termination of the clinical trial will be if

- the risk-benefit ratio for patients has changed significantly,
- the use of one of the surgical procedures is no longer justifiable,
- the sponsor deems it necessary to discontinue the clinical trial for safety reasons (e.g. on the advice of the DSMC),
- the clinical trial proves to be unfeasible.

The sponsor decides on the termination of the study in agreement with the LKP.

#### **4.6. Treatments**

##### **4.6.1. Treatments used**

Patients with bilateral inguinal hernias will undergo an operation that corresponds to routine laparoscopic hernia surgery (TAPP or TEP) and is performed according to the guidelines of the IEHS (International Endohernia Society) after consenting to participate in the study. The only deviation is that one side is specifically treated with one side is supplied with a synthetic mesh material and the other with biological mesh material. Randomisation is used to decide which side is supplied with the biological mesh material. The other side is then supplied with the synthetic counterpart. Both sides must be treated using the same technique (TAPP or TEP). The implant remains permanently in the body or, in the case of the biological mesh material, is replaced by the body's own tissue; follow-up treatment is not normally necessary.

#### 4.6.2. Description of the medical device

The aim of this study is not to specifically investigate the effectiveness of a single manufacturer's mesh, but to show whether there is a general advantage for biological mesh material over synthetic mesh material in everyday use. Meshes from different manufacturers are available for both study arms. Only CE-certified meshes will be authorised. The synthetic mesh materials should be made of polypropylene, polyester or PVDF, have large pores and be lightweight ( $< 100 \text{ g/m}^2$ ). The biological mesh materials should consist of a perforated, non-crosslinked, acellular and collagenous matrix. The mesh sizes used should be at least 10x15 cm. The meshes can be fixed with adhesive.

In addition, the participating centres should use the meshes that is also used in their clinical routine or that they would order under the conditions, on the condition that this merchandise has a valid CE certificate for the required purpose.

Form of application:                      Laparoscopic implantation according to IEHS guidelines

##### *4.6.2.1. Labelling of the medical device*

As commercial goods are used, no separate labelling is required..

##### *4.6.2.2. Storage of the medical device*

The storage conditions are to be taken from the application information of the commercial product used by each centre.

#### 4.6.3. Method for assigning patients to the treatment groups and blinding

All patients included in the study are assigned a unique patient identifier. This consists of the abbreviation of the trial centre and the consecutive number of the included patient. As all included patients have a bilateral hernia, the randomisation only has to determine which side is operated on and how. The patient is therefore represented in both study groups, with one hernia in each study arm. Randomisation is therefore only between the following two options: "Right side biological and left side synthetic mesh" and "Left side biological and right side synthetic mesh".

Before the start of the study, the biometrician creates a randomisation list for each centre, which assigns the mesh material to the respective treatment side (right/left). Randomisation is stratified by centre and performed as block randomisation (block size 6-10). The randomisation results are announced centrally by telephone by the secretariat of the LKP in Cologne-Merheim ([name]) during regular working hours (elective procedure) in order to monitor the

progress of the study permanently and to be able to unblind the patient in the event of a recurrence (see below). The person entrusted with this task is not involved in the further steps of the study (e.g. follow-up).

As the surgical technique is identical for both sides, it is not possible to be unblinded from the outside by different scars or dressings postoperatively. Both the patient and the hospital staff (except the surgeon) are therefore blinded.

The surgeon cannot necessarily be blinded. Therefore, the follow-up should not be carried out by the surgeon (possibly by someone else from the surgical team).

In the event of a hernia recurrence that necessitates a reoperation, the affected side is unblinded by telephone by the LKP secretariat to enable adequate preparation for the operation. This automatically unblinds the unaffected side as well. When a hernia occurs, the study endpoint is reached for this hernia, but not for the patient. As long as the other side has not yet developed a recurrence, the patient remains in the study with the other hernia. Only when the other hernia also develops a recurrence is this patient's participation in the study terminated.

#### 4.6.4. Previous therapy and concomitant therapy

Given the existing indication and elective surgery, this point is irrelevant for the study. Any contraindications are listed in the exclusion criteria.

##### *4.6.4.1. Alternative therapy in an emergency*

As these are elective procedures, no emergencies requiring special alternative therapies are to be expected. Any recurrences are treated as described under 4.4.1.

#### 4.6.5. Further treatment after the end of the clinical trial

In principle, the patient is already recovered after discharge and no further treatment is necessary (see also 4.6.1).

### **4.7. Efficacy and safety parameters**

#### 4.7.1. Measurement of efficacy and safety parameters

##### *4.7.1.1. Primary and secondary outcomes*

Pain reduction is measured postoperatively and during follow-up examinations using the 0-10 point visual analogue scale (VAS). Each side of the operation is documented separately. Pain

recording is also limited to the groin area so as not to impair data quality due to other sources of pain (headache and back pain, for example). As with pain recording, the recurrence rate is also recorded separately for each side. In the event of a recurrence, the result of a clinical examination must be confirmed diagnostically (ultrasound/CT/MRI). In the absence of follow-up examinations, the LOCF principle (Last Observation Carried Forward) is applied. The recurrence rate requires at least the data from the 6-month follow-up.

#### 4.7.1.2. Further outcomes

In addition to pain and recurrence rates, complications and patient satisfaction are also recorded. For this purpose, the type and number of complications (see also 4.9.1 and 2.3) are analysed, separately for each side where appropriate. The evaluation is performed using the McNemar test for the event rate in paired data.

For patient satisfaction, a side-by-side, descriptive evaluation of the assessment of the overall result, the foreign body sensation and the occurrence of paraesthesia is carried out.

#### 4.7.1.3. Safety analysis

After discharge and after the follow-up visits of a patient, the study centre must inform the LKP/study management promptly (within 7 days) of any complications that have occurred. In the event of a conspicuous accumulation of complications, the LKP together with the DSMC will assess whether these are (serious) adverse effects of the products (ADE or SADE) and whether the conduct of the study should be changed or the study terminated prematurely if necessary

#### 4.7.1.4. Description of the individual visits

**Table 2 Flow Chart**

|                                  |           |                                       | Behandlung    |                        |                                                                                                                                                          |
|----------------------------------|-----------|---------------------------------------|---------------|------------------------|----------------------------------------------------------------------------------------------------------------------------------------------------------|
|                                  | Screening | Preoperative preparation  | Surgery
D1 | Discharge  | Follow-Up
1 Week +/- 72h
6 Months +/- 4 Weeks
12 Months +/- 2 Months
24 Months +/- 2 Months
5 Years +/- 2 Months
10 Years +/- 2 Months |
| Patient identification           | X         |                                       |               |                        |                                                                                                                                                          |
| Information                      |           | X                                     |               |                        |                                                                                                                                                          |
| Informed Consent                 |           | X                                     |               |                        |                                                                                                                                                          |
| Pain: VAS (0-10), side-separated | X         | X                                     |               | X                      | X                                                                                                                                                        |
| Randomisation                    |           | X                                     |               |                        |                                                                                                                                                          |

|                               |                  |                  |   |                  |                  |
|-------------------------------|------------------|------------------|---|------------------|------------------|
| Surgery                       |                  |                  | X |                  |                  |
| Imaging (Sonography, MRI, CT) | (X)  | (X)  |   | (X)  | (X)  |
| Complications                 |                  |                  | X | X                | X                |
| Recurrence                    |                  |                  |   | X                | X                |
| Wound infections              |                  |                  |   | X                | X                |
| Haematoma/Seroma              |                  |                  |   | X                | X                |
| Patient satisfaction          |                  |                  |   |                  | X                |

In case of suspected recurrence

These measures are not mandatory for the study and are carried out if requested by the surgeon or anaesthetist. The necessity results from the patient's risk profile.

No time limits are for preoperative preparation and discharge.

### Screening-Visit

The screening visit takes place as part of the clinical routine, during which a patient routinely presents in the consultation, the emergency outpatient department or as part of a consultation. If the patient fulfils the inclusion criteria (all examinations that lead to a diagnosis correspond to the clinical routine), initial information about the study and the planned surgical procedure (TEP or TAPP) is provided. The patient receives an appointment for surgery regardless of participation in the study. In addition, an initial side-separated pain assessment is carried out using VAS. If necessary, an imaging procedure (sonography/CT/MRI) is also performed to support the diagnosis. However, this is independent of participation in the study and is part of routine clinical practice.

### Preoperative preparation (D-3 bis D-1)

The patient comes to the clinic for routine surgery preparation (3-1 days before the operation). A written declaration of consent for the operation and anaesthesia is mandatory. Optional laboratory tests (e.g. small blood count, electrolytes, Quick/INR/PTT, creatinine, CRP, TSH) can be carried out if requested by the surgeon or anaesthetist (the sole use of a biomesh does not require a blood sample, the necessity is determined by the patient's risk profile).

However, the patient is also informed about the study by the investigator or a medical member of the study group and asked for consent to participate in the study.

If consent is given, a randomisation list drawn up in advance is used to allocate which side will be supplied with the biological mesh by telephoning the LKP secretariat. The other side then automatically receives the synthetic mesh.

### Surgery (D1)

The operation must be standardised in accordance with the "Guidelines for laparoscopic (TAPP) and endoscopic (TEP) treatment of inguinal hernia" published by the International Endohernia Society (IEHS). This is ensured by the fact that only hernia centres participate in the study.

Both sides must be treated with the same surgical procedure (TEP or TAPP), the only difference being the mesh used (biomesh or synthetic mesh).

Complications are recorded for the first time (see also 2.3 and 4.9.1.3)

### **Hospital discharge**

On the day of discharge, pain is again recorded using VAS and any complications are documented. If the patient's profile makes it necessary, additional imaging procedures are carried out. This is not mandatory for study reasons, but will be documented if available.

The use of a biomesh is not expected to prolong hospitalisation.

### **Follow-up (1 week +/- 72h, 6 months +/- 4 weeks, 12 months +/- 2 months, 24 months +/- 2 months, 5 und 10 years +/- 2 months postoperative)**

A clinical examination is performed and pain is assessed separately on each side using the VAS (visual analogue scale 0-10). In addition, the presence of a recurrence is evaluated. In the event of a suspected clinical recurrence, confirmation should be made by means of sonography, MRI or CT, which also corresponds to clinical routine.

The incidence of pain after 6 months and the occurrence of a recurrence within the first two years are the two primary endpoints.

Patients can optionally consent to further follow-up visits five and ten years after the operation. The examinations correspond to those of the earlier follow-up visits. If the patients no longer live at the location of the trial centre after ten years, they can be contacted by telephone and asked about the occurrence of recurrences.

The following are also collected

- Complications (e.g. revision surgery, mesh dislocation, haemorrhage)
- Wound infections
- Haematoma/ Seroma

- Patient satisfaction (overall result, foreign body sensation, paraesthesia)

#### Duration of the clinical trial in the individual patient

The inpatient stay for the patient is usually completed after 1-6 days; due to the necessary follow-up examinations, the total duration of the study for each patient is approx. 2 years. At the follow-up examination two years after the operation, the patient can decide whether they would like to take part in further check-ups, which take place five and ten years after the operation. If the patient agrees to further participation in the study, the entire study lasts for the patient until a recurrence occurs on both sides, but for a maximum of ten years.

#### 4.7.2. Appropriateness of the measurement methods

The primary objective is to investigate whether a significant reduction in pain intensity can be demonstrated when a biological mesh is used instead of a synthetic mesh for the treatment of inguinal hernias. This requires a rational assessment of subjective pain intensity, as can be achieved with the commonly used visual analogue scale (VAS). At the same time, it should be shown that the biological mesh is not inferior in terms of recurrence and/or procedure-related complications. To this end, it is necessary to determine the recurrence rate and to record the type and number of complications that occur.

The self-controlling design of this study allows an ideal comparison between the two mesh materials. As only patients with bilateral hernias are included and one of the two meshes is inserted on each side (using the same surgical technique, the patient is blinded), each patient is simultaneously their own control. This enables a comparison that is almost completely unaffected by other influences such as comorbidity, age, gender or experience of the surgeon.

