**Safety:**

Complications are compared with the McNemar test for the event rate in paired data.

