## **2. Aims of the clinical trial**

The aim is to show that the use of biological mesh material for the laparoscopic treatment of inguinal hernias causes significantly less pain postoperatively than the use of synthetic mesh material (superiority), without an increased recurrence rate (non-inferiority).

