## **2.3. Secondary outcome**

- Intensity of pain at other time points (see table Flow Chart)
- Recurrence rates within one year after surgery
- Complications e.g. infections, mesh dislocations
- Haematoma
- Seroma
- Patient satisfaction (overall result, foreign body sensation, paraesthesia) at various points in time (see table flow chart)

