#### 6.1.4. Secondary outcomes

The secondary outcomes are presented descriptively and compared exploratively. The recurrences are visualised using Kaplan-Meier curves.

Complications are compared in the as-treated collectives.

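### Section 4.7.2 extends the non-inferiority goal to complications, which the rest of the protocol treats as exploratory and tests only with McNemar

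*Protocol*

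**What the plan says.** Section 4.7.2 justifies the measurement methods. After the pain objective it adds a second goal: "it should be shown that the biological mesh is not inferior in terms of recurrence and/or procedure-related complications". It then names the means: "To this end, it is necessary to determine the recurrence rate and to record the type and number of complications that occur".

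The analysis of complications is given in three places:

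- Synopsis, Safety: "Complications are compared with the McNemar test for the event rate in paired data".
- Section 4.7.1.2: "The evaluation is performed using the McNemar test for the event rate in paired data".
- Section 6.1.4: "Complications are compared in the as-treated collectives".

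Their status is secondary. Section 2.3 lists "Complications e.g. infections, mesh dislocations", and section 6.1.4 says "The secondary outcomes are presented descriptively and compared exploratively".

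The formal aim in section 2 ties non-inferiority to recurrence: "without an increased recurrence rate (non-inferiority". The primary objective in the synopsis and section 2.2 do the same. Section 6.1.3 sets the only margin (+3 percentage points) and the only confidence-interval rule, both for recurrence.

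**The concern.** A goal of showing non-inferiority needs a margin and a rule that compares a confidence limit with it. For complications the protocol has neither. McNemar's null hypothesis is that the two sides have equal rates. Failing to reject it says only that the data are compatible with equality, and they may be equally compatible with a material excess on the biological side. The goal in 4.7.2 and the planned analysis therefore do not fit.

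The and/or in that sentence adds a second difficulty. Taken alone, it leaves open whether complications are a further claim or an alternative to recurrence.

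At stake is the wording of the safety conclusion. Complications are the protocol's own safety criterion in the synopsis, and a report that followed 4.7.2 could describe the biological mesh as not inferior in complications without an analysis that supports this.

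**Working it through.** **1. The places side by side.**

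| Place in protocol | Recurrence | Complications |
|---|---|---|
| Synopsis (primary objective), 2, 2.2 | Non-inferiority | No hypothesis |
| 2.3, 6.1.4 | One-year rates secondary | Secondary, exploratory |
| 6.1.3 | Margin +3 points, 95 % CI rule | Nothing |
| 6.1.5 | Drives the sample size | Nothing |
| Synopsis (Safety), 4.7.1.2 | – | McNemar |
| 4.7.2 | To be shown not inferior | To be shown not inferior, joined by and/or |

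Only 4.7.2 attaches a non-inferiority goal to complications.

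**2. The protocol's own sizing.** Section 6.1.5 gives 203 and 451 cases, and 496 after loss. With n = (1.96/h)² × p(1 − p) and p = 0.05:

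- h = 0.03: 4268.4 × 0.0475 = 202.8 (stated 203).
- h = 0.02: 9604 × 0.0475 = 456.2 (stated 451, close).
- 451 × 1.1 = 496.1 (stated 496).

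All of these concern recurrence. No rate, margin, power or sample size is given for complications.

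**3. What a non-significant McNemar result would mean (illustration).** Assumptions, none of them from the protocol: the complication rates, two-sided alpha 0.05, and independence of the two sides within a patient. The number of pairs is 446 (496 × 0.9 = 446.4).

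Let p_s and p_b be the synthetic and biological rates. Then:

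- Biological side only: b = p_b(1 − p_s).
- Synthetic side only: c = p_s(1 − p_b).
- d = b − c and s = b + c.
- Power ≈ Φ{[d√n − 1.96√s] / √(s − d²)}.
- 95 % CI half-width = 1.96 √[(s − d²)/n].

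| p_s vs p_b | b | c | Power, n = 446 | Half-width (points) |
|---|---|---|---|---|
| 3 % vs 6 % | 0.0582 | 0.0282 | 58 % | 2.71 |
| 5 % vs 8 % | 0.0760 | 0.0460 | 44 % | 3.23 |
| 2 % vs 4 % | 0.0392 | 0.0192 | 42 % | 2.24 |

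**4. Sensitivity.**

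- The exact McNemar test at 451 pairs is non-significant with probability 47 %, 60 % and 66 % in the same three cases, so its power is lower (53 %, 40 %, 34 %).
- A within-patient correlation of 0.2 raises the approximate power at n = 446 to 67 % for 3 % vs 6 % and 52 % for 5 % vs 8 %.
- At n = 496 with correlation 0.2 these become 71 % and 57 %.

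**5. One data set.** Take 451 pairs, 30 with a complication only on the biological side and 17 only on the synthetic side.

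- Exact McNemar p = 0.079.
- Difference = (30 − 17)/451 = +2.9 points.
- SE = √(47 − 13²/451)/451 = 1.51 points.
- 95 % CI: −0.1 to +5.8 points.

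The test is non-significant, yet an excess of nearly 6 points is not excluded. The interval shows this and the p-value does not.

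**The case against.** The strongest reply is that the protocol makes no formal non-inferiority claim for complications. The sentence stands in a section on measurement methods and leads to a conclusion about what must be recorded. Every place that fixes objectives or decision rules limits non-inferiority to recurrence, which also settles what the and/or leaves open. For a secondary, exploratory outcome, McNemar on paired event rates is a suitable test. All of this stands, and it is why the point is one of wording.

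A reader might infer that a non-significant McNemar result is planned as proof of safety, or would be its only support. The documents do not say so. They also plan side-specific analysis of the type and number of complications (4.7.1.2), as-treated reporting (6.1.1, 6.1.4) and review with the DSMC (3.4, 4.7.1.3).

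A reader might also take the power figures as a defect in the trial's size. They are not: the rates are assumed, and the trial was never sized for complications. Complications recorded at surgery and discharge do not depend on two-year follow-up, so the number of pairs could approach 496. In the 3 % vs 6 % case the test detects the excess more often than not.

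Finally, interval reporting may already be in the statistical analysis plan, which is not shown. That part of the fix is therefore an improvement, and its absence from the protocol is not an error. The mismatch remains, because the protocol itself states both the goal and the test.

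**Conclusion.** The point holds as a minor internal inconsistency. One sentence in 4.7.2 sets a non-inferiority goal for complications that the formal aims do not contain and that the planned McNemar test, without a margin or interval rule, cannot meet. This conclusion rests on the text alone.

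The primary endpoints, the recurrence margin and the sample size are untouched. The practical effect is confined to what may be concluded on safety. The figures only illustrate why non-significance should not be read as non-inferiority. They depend on assumed complication rates, alpha and within-patient correlation, and approximate power in the cases shown runs from about 42 % to 71 %.

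**What to change.** 1. **Section 4.7.2:** limit the non-inferiority statement to recurrence, and describe complications as an exploratory safety comparison. Recording their type and number stays as it is.
2. **Section 4.7.1.2 and synopsis (Safety):** for complications that can be assigned to a side, report the paired risk difference (biological − synthetic) with a two-sided 95 % CI alongside the McNemar p-value.
3. **Same places:** state that a non-significant result is not read as non-inferiority.

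If the sponsor does want a non-inferiority claim for complications, the protocol would instead have to define the complication endpoint, a justified margin and a paired confidence-interval rule. The documents give no basis for choosing that margin.

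The cost is wording in three places, one extra interval per complication, and a more cautious safety statement. No new data or patients are needed.
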